### **Primary Analysis**

#### **o Population**

The ARISTOTLE trial used an intent to treat (ITT) approach for the primary efficacy analysis, and an on-treatment approach for the sensitivity analyses and safety outcomes. To perform an equivalent analysis with the EHR data the following analysis populations will be used for all objectives:

Prescribed Population: all patients who were prescribed a treatment, regardless of future changes to treatment.

When summarizing data using this population, subjects are categorized according to the As Prescribed group.

On-treatment Population: all patients who were prescribed a treatment. In the case of patients discontinuing or switching treatment, data will be included up to and including their derived date of last dose of the initially prescribed treatment.

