##### Date of last dose (all objectives)

The date of last dose will be estimated using the subject's date of prescription, number of tablets prescribed, and daily dose. Where there are missing values for the number of tablets prescribed or daily dose suitable values will be used to replace these, for example by substituting with the median or modal value. To allow for stockpiling of tablets and less than 100% adherence we will add 30 days after the apparent end of treatment when deriving date of last dose.

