##### Supportive censoring scheme:

Patients will be censored at the earliest of: outcome of interest, death date, 'transferred out date', 'last collection date', 5 years after the index date, or the derived last date of study drug. By censoring around the time of last study drug this scheme should include only events likely to be due to the drug taken.

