### Secondary analyses

Secondary outcomes include the key safety outcome of major bleeding (as defined in section N) and the individual outcomes of stroke, systemic embolism, myocardial infarction, and mortality. All secondary outcomes other than major bleeding will use the same analysis approach (primary censoring scheme and regression model) as specified for the primary analysis above. For major bleeding the same regression model as the primary analysis will be used but with the supportive censoring scheme in which patients are censored around the time of last study drug. Within major bleeding results will also be summarised for intracranial, gastrointestinal, and bleeding at other locations. This safety analysis approach will be used for all 3 objectives.

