##### **Missing Prescription Data**

Treatment may be initiated in secondary care meaning the first prescription of patients newly initiating treatment is missing. To account for these potentially missing first prescriptions we will perform a sensitivity analysis where those newly initiating treatment are assumed to have a missing earlier prescription and therefore assigned an earlier derived index date. Patients who are hospitalised may also have prescriptions issued in secondary care leading to treatment gaps seen in their primary care prescription data. The primary analysis using the Prescribed Population will not be affected by such gaps as patient time is included until the patient is censored or experiences an event regardless of treatment gaps. The supplementary analysis using the On-treatment Population and the safety analysis censor at derived date of last dose and may therefore miss events whilst a patient was on treatment in hospital. We will investigate the occurrence of hospitalisation around treatment discontinuation and assess the potential impact on the results of such missed events by performing a sensitivity analysis with different extended derived dates of last dose (extending the final period to 60 or 90 days after the final prescription estimated end).

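### In the on-treatment scheme, a patient who switches directly is followed for at least 30 days on the new anticoagulant as if still on the old one; this affects the only planned major-bleeding analysis

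*Protocol*

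**What the plan says.** All of the following is in the Protocol.

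- **Section O, Population.** The On-treatment Population treats stopping and switching alike: "data will be included up to and including their derived date of last dose of the initially prescribed treatment".
- **Section O, Date of last dose.** That date comes from the initial drug's own prescriptions: "The date of last dose will be estimated using the subject's date of prescription, number of tablets prescribed, and daily dose". Then "we will add 30 days after the apparent end of treatment when deriving date of last dose". The reasons given are stockpiling and incomplete adherence.
- **Section O, Supportive censoring scheme.** The list of censoring events ends with "5 years after the index date, or the derived last date of study drug". Neither a switch nor the start of another anticoagulant is listed. The stated purpose is: "By censoring around the time of last study drug this scheme should include only events likely to be due to the drug taken".
- **Section Q, Missing Prescription Data.** A sensitivity analysis lengthens the window, "extending the final period to 60 or 90 days after the final prescription estimated end", with no exception for switchers.
- **Section O, Secondary analyses.** Major bleeding is analysed "with the supportive censoring scheme in which patients are censored around the time of last study drug", for all three objectives. No bleeding analysis under the primary scheme is planned.
- **Section O, Sensitivity analyses.** Stroke/systemic embolism, myocardial infarction and mortality are repeated under the same scheme.

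**The concern.** The added 30 days are reasonable for a patient whose prescriptions simply stop, who may still have tablets in hand. They do not fit a patient whose record shows a replacement anticoagulant. For that patient the window is time on the comparator drug, or on another anticoagulant in Objective 3, and any event in it is charged to the drug that was left.

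What is at stake is the bleeding comparison, which has no other planned analysis, and the on-treatment efficacy results, which are meant to show whether discontinuation undermines the primary findings. The 60- and 90-day variants do not test the problem; they lengthen it.

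Section L (end of Objective 1) adds a complication: a patient's warfarin period and later apixaban period may both enter the cohort. A bleed shortly after such a switch could then count once in each arm.

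**Working it through.** The plan states no figure on this point, so there is nothing to reproduce. The check traces the rule and then shows its possible size under stated assumptions.

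**Step 1: days charged to the old drug.** Call a switch direct if the new drug is first prescribed on or before the apparent end of the old one. Unless follow-up ends sooner for another reason:

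post-switch days = leftover supply + added days

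If the apparent end of treatment is taken as the switch date, leftover supply is 0. If it is taken as exhaustion of supply, leftover supply is whatever remained; 0–28 days is assumed here.

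| Rule | Post-switch days |
|---|---|
| 30 days (main) | 30–58 |
| 60 days (sensitivity) | 60–88 |
| 90 days (sensitivity) | 90–118 |

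Even the kinder reading leaves 30 days. A patient who starts the new drug after a gap of g days (g below 30) has 30 − g days under the main rule. A patient who starts after the window has none.

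**Step 2: share of an arm's on-treatment events that occur after the switch.** Let T be mean true on-treatment days, s the proportion switching, d the post-switch days, and k the event rate after the switch relative to the old drug's rate.

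share = s·d·k / (T + s·d·k)

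Assumed, not in the documents: T = 548, s = 0.2–0.4, 28 leftover days, k = 1 or 3.

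| d | k | s = 0.2 | s = 0.4 |
|---|---|---|---|
| 58 (30 + 28) | 1 | 11.6/559.6 = 2.1% | 23.2/571.2 = 4.1% |
| 58 | 3 | 34.8/582.8 = 6.0% | 69.6/617.6 = 11.3% |
| 118 (90 + 28) | 1 | 23.6/571.6 = 4.1% | 47.2/595.2 = 7.9% |
| 118 | 3 | 70.8/618.8 = 11.4% | 141.6/689.6 = 20.5% |

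With no leftover supply (d = 30) the first two rows become 1.1–2.1% and 3.2–6.2%.

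**Step 3: effect on the hazard ratio.** A share of relabelled events is not a bias. The arm's observed rate is multiplied by (T + s·d·k)/(T + s·d). Section O's stroke/systemic embolism hazard ratio of 0.79 serves only as a stand-in for the true value. With d = 58 and switching from warfarin only:

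- k = 1: the factor is 1 and the hazard ratio stays at 0.79.
- k = 0.79 (the patient takes on apixaban's rate), s = 0.4: factor 566.3/571.2 = 0.991, hazard ratio 0.797, slightly toward 1.
- k = 3: factor 582.8/559.6 = 1.041 at s = 0.2 and 617.6/571.2 = 1.081 at s = 0.4; hazard ratio 0.76 and 0.73, away from 1.

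A two-arm version assumes that 10–50% of the warfarin arm and 5% of the apixaban arm switch, 1–2 years' mean time on drug, and a post-switch rate 1 or 3 times the new drug's usual rate. The observed hazard ratio is then 0.733–0.804 with 30–58 post-switch days, and extends to 0.693–0.817 at 118 days. With 10% of the warfarin arm switching and 30–58 days, it stays within 0.790–0.794.

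**Step 4: length of overlap by arm.** Section O (Sensitivity analyses) says warfarin daily dose is poorly recorded, and the last-dose rule replaces missing doses with substituted values. The warfarin supply end will therefore often rest on imputation, and the overlap may differ in length between arms.

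**The case against.** The strongest counter-arguments are these.

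- **The main conclusions do not depend on this.** This stands. Non-inferiority and superiority conclusions rest on the primary censoring scheme, which ignores treatment changes by design, and the validation criteria concern that primary outcome. A reader might infer that the comparison with ARISTOTLE is compromised; it is not.
- **The direction is not fixed.** This stands. A reader might infer that mixing the drugs must pull the contrast toward no difference. Step 3 shows no movement, movement toward 1, or movement away from 1, depending on the rate just after a switch.
- **Switching is examined elsewhere.** This stands in part. A reader might take the on-treatment scheme to be the only planned check. Section O (Sensitivity analyses) also commits to describing patients who switch or stop, and allows inverse-probability-of-censoring weighting or a rank-preserving structural failure time model. The description changes no estimate and the models are optional. Neither cuts bleeding follow-up at the switch.
- **The stated aim is hedged.** This stands in part. It would be too strong to say that the aim fails for every switcher: one who starts the new drug after the window, or has no event in it, adds no misattributed event.
- **A patient going from warfarin to apixaban and back might seem to be counted on warfarin throughout.** The documents do not say this. Section L, Step 2 ties warfarin person-time to its eligibility period, and warfarin periods after apixaban are barred from the Objective 1 warfarin cohort. Those are entry rules, but nothing says prescriptions either side of a switch are joined.
- **A carry-over window is a legitimate choice, and derivation details may sit in an analysis plan not shown.** A carry-over window can be defended, but this protocol offers no such argument, and its own reasons for the added days do not apply after a replacement is prescribed. The protocol itself fixes the end point for switchers and the censoring list, so the point does not depend on unseen detail.

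**Conclusion.** The point holds for the on-treatment scheme. As written, a direct switcher contributes at least 30 days on the new anticoagulant to the old drug's record, 60 or 90 days in the sensitivity variants, and leftover supply on top if the end of treatment means exhaustion of supply. That contradicts the scheme's own purpose, in the sole major-bleeding analysis for all objectives and in the on-treatment efficacy analyses.

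The overlap in days follows from the text, apart from the assumed 0–28 days of leftover supply. The consequence for the estimates does not: switching frequency, time on drug and post-switch event rate are all assumed. The 2–4% and 6–11% shares under the main rule are illustrations of relabelled events, not estimates of bias; the threefold rate in particular has no support in the documents. The bias may be small, and its sign is unknown. The case for acting is that bleeding has no other planned analysis and the correction is cheap.

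**What to change.** In Section O (Population, Date of last dose, Supportive censoring scheme) and Section Q (Missing Prescription Data), end on-treatment follow-up at the earlier of:

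1. the derived last dose, including the added days; and
2. the day before the first prescription of a different oral anticoagulant.

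The 30-, 60- and 90-day additions then never run past a recorded switch, and misattributed time after the recorded switch date falls to 0 days. The overlap that lets one bleed count in both arms goes too. If a short carry-over window after a switch is wanted, specify and justify it separately as a sensitivity analysis.

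The cost is one sentence in each place, using prescription dates already needed to identify switchers. A little person-time and a few transition-period events leave the on-treatment analyses. The prescription date is taken as the switch date, so a new anticoagulant started in hospital, which Section Q acknowledges can go unrecorded, would still be picked up late. The change does not remove selection from censoring at a switch; the planned description of switchers and the optional weighting remain relevant to that.

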##### Primary censoring scheme:

Patients will be censored at the earliest of: outcome of interest, death date, 'transferred out date', 'last collection date', or 5 years after the index date. The 5-year limit reflects the maximum possible follow-up for a subject in the ARISTOTLE trial. Conclusions regarding noninferiority or superiority will be based on the results of the analyses using this censoring scheme as this most closely resembles the ARISTOTLE analysis plan.

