**K. Planned use of linked data (if applicable):**

We intend to use CPRD data linked with HES in patient data to enable optimal stroke, MI, and major bleeding ascertainment, and ONS mortality data to determine deaths. When matching CPRD patients we plan to include the practice level deprivation level index as a matching variable because socioeconomic status is predicted to influence the likelihood of the primary study outcome of stroke.

[figure not shown]

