## L. Definition of the Study population

For all objectives two datasets of UK primary care data will be combined: CPRD Gold and CPRD Aurum. Patients with a prescription for an oral anticoagulant in the time period 01 January 2013 to 31 January 2019 (exact cut-off date dependent on date of final data extracts) and a prior diagnosis of atrial fibrillation will be selected as the EHR cohort. Apixaban gained UK marketing authorisation in January 2013 for the indication of prevention of stroke and systemic embolism in AF patients; the minimum date is set to capture all patients prescribed apixaban for this indication in the UK. A previous study validated the use of diagnostic read codes for identifying patients with AF in CPRD by sending surveys to GPs and found a confirmation rate of 98% among patients originally identified with AF codes.

### Objective 1

**Step 1:** We will select all (HES and ONS linked) patients in the EHR cohort who would have met the following eligibility criteria for inclusion in the ARISTOTLE study, at least 6 months after patient registration in an up to standard practice: or 6 months post-UTS date, whichever is later:

- a diagnosis of AF,
- age over 18 years,
- at least one of the following risk factors for stroke: diagnosis of congestive heart failure, hypertension requiring pharmacological treatment, age greater than 75, diabetes mellitus, and prior stroke or systemic embolism,
- no AF due to reversible causes (e.g. thyrotoxicosis, pericarditis),
- no clinically significant (moderate or severe) mitral stenosis, in EHRs clinical significance and severity are not consistently recorded therefore a diagnosis of mitral stenosis will be sufficient to exclude a patient,
- no increased bleeding risk that is believed to be a contraindication to oral anticoagulation (e.g. previous intracranial haemorrhage),
- no conditions other than AF that require chronic anticoagulation (e.g. prosthetic mechanical heart valve),
- no persistent, uncontrolled hypertension (systolic BP > 180 mm Hg, or diastolic BP > 100 mm Hg), in EHRs this will be implemented by excluding patients whose latest blood pressure reading in the 6 months prior to the index date is over the systolic or diastolic blood pressure limit
- no active infective endocarditis,
- no concomitant treatment with aspirin > 165 mg/day,
- no simultaneous treatment with both aspirin and a thienopyridine (e.g., clopidogrel, ticlopidine),

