#### **N. Exposures, Outcomes and Covariates**

The exposures of interest are apixaban, warfarin, rivaroxaban, and dabigatran (any dose for each exposure).

The individual effectiveness outcomes:

- stroke
- systemic embolism
- myocardial infarction
- all cause death

The safety outcome for the study:

- major bleeding (bleeding requiring transfusion, bleeding at a critical site, bleeding requiring attendance at hospital, or fatal bleeding)

For all outcomes we make the assumption that if there is no record of an outcome then the outcome did not occur.

The EHR ARISTOTLE-eligible patients prescribed apixaban will be matched to the ARISTOTLE apixaban patients on the variables listed in section L (step 3 of objective 1), with value taken at baseline (value at time of first dose or latest measurement/data recorded prior to first dose).

When matching between the treatment arms within the EHR cohort of patients the variables to be considered for inclusion in the matching algorithm include those listed in section L used in matching from the EHR treatment arm to the trial patient data in addition to EHR variables such as data source (CPRD Gold or Aurum), socioeconomic status, and comorbidities.

[figure not shown]

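### Both censoring lists run past the possible end of HES/ONS coverage, so late follow-up may be under-ascertained and the hazard ratio may drift toward apixaban

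*Protocol*

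**What the plan says.** **Sources.** Protocol section K states: "We intend to use CPRD data linked with HES in patient data to enable optimal stroke, MI, and major bleeding ascertainment". It names ONS mortality data for deaths.

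**Missing records.** Section N assumes, for every outcome, that "if there is no record of an outcome then the outcome did not occur".

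**End of follow-up.** The primary censoring scheme in section O opens with "Patients will be censored at the earliest of: outcome of interest, death date"; the other end points it names are transfer out of the practice, the practice's last data collection and a five-year cap. The supportive scheme, which governs major bleeding and the on-treatment analyses, repeats this list and ends with "5 years after the index date, or the derived last date of study drug". Both lists are closed, and neither contains the end of HES or ONS coverage. Section O bases its non-inferiority and superiority conclusions on the primary scheme and applies it to the primary outcome of all three objectives.

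**Who is linked.** For Objective 1, section L says: "We will select all (HES and ONS linked) patients in the EHR cohort". Section Q (Missing Outcome Data), however, presents the restriction to linked patients as a sensitivity analysis that repeats the primary analysis. It expects recording to be better in the linked cohort.

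**Start of follow-up in one sensitivity analysis.** In section Q (Missing Prescription Data), new initiators are "assumed to have a missing earlier prescription and therefore assigned an earlier derived index date". The length of the shift is not given, nor is a rule for events in the added interval.

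**The concern.** If HES or ONS coverage ends before a practice's last collection date, patients stay at risk while one of the planned outcome sources is silent. Section N then turns that silence into event-free time, so absolute rates are too low in both arms.

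The hazard ratio is affected only if the arms carry different amounts of this time. Section P says apixaban was newly available in the study period. Section O defines the comparison as starting apixaban against starting or continuing warfarin, so warfarin patients can be indexed from January 2013. Index date is not among the matching variables that sections L and N list. Late calendar time may therefore be richer in apixaban follow-up, which would move the HR downward.

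At stake is the validation step. Criterion 1 in section O requires an HR between 0.69 and 0.99, and the result helps decide whether the method is carried over to patients outside the trial. The linked-cohort sensitivity analysis in section Q does not protect against this, because it repeats the primary analysis with the same censoring rule.

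**Working it through.** No figure in the protocol rests on the censoring rule, so there is no stated number to reproduce. The check is what the rule does as written.

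**From the protocol:** entry from 01 January 2013 to 31 January 2019 (6.08 years, end provisional) and a 5-year cap (sections L and O).

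**Assumed, not in the documents:**
- follow-up ends at 6.08 years for everyone;
- linkage ends 3, 6 or 12 months before that;
- a fraction h = 0.3 to 0.5 of events is seen only in linked data, so GP records still capture 50-70%;
- hazards are constant and there is no other loss;
- apixaban entry rises linearly;
- warfarin entry is either uniform, or 70% in the first three months of 2013 with the rest uniform.

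**Formula.** Observed rate = true rate × (1 − h × u), where u is the share of the arm's person-time after coverage ends. Hence

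observed HR = true HR × (1 − h·u_apixaban) / (1 − h·u_warfarin).

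Example, 6-month gap, uniform warfarin entry, h = 0.5, true HR 1.00: (1 − 0.5 × 0.2235) / (1 − 0.5 × 0.1397) = 0.888 / 0.930 = 0.955.

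| Gap | u apixaban | u warfarin, uniform | HR, h = 0.3 / 0.5 | u warfarin, 70% early | HR, h = 0.3 / 0.5 |
|---|---|---|---|---|---|
| 3 months | 11.6% | 7.0% | 0.986 / 0.976 | 1.4% | 0.969 / 0.949 |
| 6 months | 22.3% | 14.0% | 0.974 / 0.955 | 2.8% | 0.941 / 0.901 |
| 12 months | 41.3% | 27.9% | 0.956 / 0.922 | 6.6% | 0.894 / 0.820 |

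**Check with the Cox model.** The expected Cox score equation was also solved with uniform warfarin entry, 8% per year attrition, a warfarin event rate of 1.6% per year and 50% GP-only capture. A true HR of 1.00 gives 0.971, 0.945 and 0.902 for the three gaps with linear apixaban uptake, and 0.948, 0.903 and 0.834 with quadratic uptake. The direction is the same and the shift somewhat larger than in the rate-ratio formula. A true HR of 0.79 with a 12-month gap becomes 0.712 (linear) or 0.659 (quadratic); the latter falls below the 0.69 limit.

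**When the bias vanishes.** With the same calendar distribution in both arms the HR stays at its true value and only rates fall. With no gap, u = 0 in both arms and nothing changes. Censoring at coverage end also sets u = 0; the Cox calculation then returned 0.790, 0.950 and 1.000 for those true values.

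**Backdated index.** A patient enters through a recorded prescription, so must be alive on that date. Any time added before it is immortal with respect to death and fatal events. Assuming no events in the added time and no adjustment for prior VKA status, a true HR of 0.79 stays 0.790 if equal shares of both arms are shifted. If all apixaban and half of warfarin patients are shifted, it becomes 0.775 (28 days) or 0.744 (90 days).

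**The case against.** The strongest reply is that the premise is not in the protocol. No HES or ONS coverage date appears, the cut-off depends on the final extracts, and without a gap there is nothing to correct. That stands, and it makes the size conditional. It does not remove the omission, because the lists are closed and would be followed as written if a gap existed.

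A reader might infer that events after coverage ends cannot be recorded at all. The protocol does not support this: section Q says only that recording is expected to be better with linkage. The fault is under-recording.

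A reader might also take the larger shifts as the expected result. They need 70% of warfarin patients to enter in early 2013, which nothing in the protocol supports. Repeat warfarin eligibility periods (section L) may spread warfarin entry over later years, and the listed matching variables are candidates that could be extended.

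Nor is a null effect landing inside 0.69-0.99 strong evidence of harm. The upper limit lies only 0.01 below 1, so sampling error can do the same.

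The backdated index touches one sensitivity analysis; the primary index date is the recorded prescription. Patients who die between hospital initiation and a GP prescription are missed in the primary analysis too, so backdating does not cause that loss. Matching on prior VKA use may equalise the shifted shares, and a non-fatal event in the added interval might still be counted.

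**Conclusion.** The point holds in a conditional form and should be fixed. Sections K, N and O together would count under-ascertained time as fully observed whenever linkage ends before last collection. Rates would then be too low, and the HR would move toward apixaban if apixaban follow-up lies later in the calendar.

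For a true HR of 1.00 the observed value would be about 0.98-0.99, 0.96-0.97 or 0.92-0.96 for gaps of 3, 6 or 12 months with uniform warfarin entry, and 0.95-0.97, 0.90-0.94 or 0.82-0.89 with 70% of warfarin entry in early 2013. Both ranges assume linear apixaban uptake and 30-50% of events seen only in linked data. The documents do not establish that a bias of any particular size will occur.

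The conflict between sections L and Q may matter more: if the main cohort includes unlinked patients, they lack HES and ONS throughout follow-up, and no end date repairs that. The backdated index is a secondary point, confined to one sensitivity analysis.

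**What to change.** 1. In section O, add the earlier of the HES and ONS coverage end dates to both the primary and the supportive list. If there is no gap, the edit changes nothing. If there is one, the cost is the uncovered person-time: under the assumptions above, about 12%, 22% or 41% of apixaban follow-up for gaps of 3, 6 or 12 months, and 7%, 14% or 28% of warfarin follow-up with uniform entry.
2. Reconcile section L (Objective 1 cohort linked) with section Q (linked cohort only as a sensitivity analysis), and state which patients the primary analysis contains.
3. In the backdated-index sensitivity analysis, keep the presumed earlier start as the time origin but begin time at risk at the first recorded prescription (delayed entry), and state the length of the shift. A fixed lag after the recorded prescription is no substitute: it discards early events and no longer tests for a missing earlier prescription. The cost is a reworded paragraph.
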